## Abstract

Depression is highly recurrent and heterogenous in its individual course, requiring a personalized treatment approach. Patients today can collect large volumes of personal data via smartphones and smartwatches and may utilize them for their treatment and self-management. We aim to provide proof-of-concept that these data can (i) serve as an objective marker of and (ii) predict the daily and weekly self-reported depression severity within individuals with depressive disorders.

In this exploratory study, 15 adult patients with depressive disorders will collect self-report and biosensor data over the course of one year. Participants will (a) attend three in-person appointments (at baseline, 6 months, and 12 months), (b) self-report daily and weekly depressive symptoms, (c) continuously collect sensor data via the “iTrackDepression” app on their Android smartphone (app usage, phone calls, phonetic parameters from voice recordings), and (d) wear a Samsung Galaxy Watch 5® to record data from the accelerometer, step sensor, light sensor, and heart rate sensor. We will apply multilevel correlations, vector-autoregressive models, and Machine Learning approaches to identify individual patterns in the data, particularly in the relationships between biosensor data and self-reported depressive symptoms.

Enhancing the understanding of individual disease trajectories through data from smartphones and smartwatches could allow for classical, digital, and self-management interventions for depression to be delivered in a manner and at a time specifically tailored to the individual's needs.

Clinical trial registration number: DRKS00032618 (https://drks.de/search/en/trial/DRKS00032618)

Depressive disorders are highly recurrent: At least 50 % of individuals who recover from a first episode of depression will have one or more additional episodes in their lifetime, and the number increases to a staggering 80 % for those with a history of two episodes [1]. Most patients with depressive disorders have an unfavorable prognosis and the majority experiences a disabling and chronic disorder [2], characterized by premature mortality [3], reduced quality of life [4], and loss of occupational functioning [5]. After acute depressive episodes have been treated, substantial, unresolved morbidity in patients with depressive disorders remains. Patients with a recurrent depressive disorder face another year to reach functional recovery after syndromal remission, which is due to residual depressive symptoms [6]. The highly recurring nature of depression and its devastating consequences for patients, their families, and the society makes the monitoring and prolonged disease management of depression an increasingly recognized priority [7]. Patients urgently require markers for monitoring their disease state and predictions about their expected disease course [8], but presently available clinical prediction models for relapse and recurrence of depression are not yet sufficiently developed for being deployed [9] and so far no clinically relevant tools for stratifying subgroups in individuals affected by depression have been established [10].

This lack of success in establishing predictive models for depression can be attributed to the highly heterogenous phenotype of depressive disorders [11]. The heterogeneity of phenotypes leads to not very informative conclusions for the individual patient, as research traditionally applied group-level statistics that are combining data from individuals with very different problems into one category [12]. Consequently, the individual patient needs to be the focus of analysis to create meaningful conclusions from their personal data [13]. The collection of rich, longitudinal datasets through ambulatory assessment (AA, using smartphones and smartwatches for data collection [14]) provides the opportunity to run statistical analyses for individual participants. In a previous study, we were able to use daily, self-reported data to reveal the specific temporal order of illness processes in single patients [15] and to create unique, personalized dynamic network models depicting the clinically well-known heterogeneity of depression [16]. These approaches may aid the identification of markers and predictors of individual disease trajectories. AA is considered less intrusive than diagnostic assessments in a laboratory or clinical environment [17] and less prone to recall bias compared to retrospective assessments [18]. However, daily self-reporting can become burdensome to participants.

Therefore, great hope for identifying markers and predictors of depressive disease trajectories has been placed in the rise of mobile sensing (MS), using build in sensors of smartphones and wearables to collect data in real time [19]. MS facilitates the collection of personal data reflecting individual behaviour and physiology that is related to depression, such as sleep [20], physical activity [21], heart rate [22], speech features [23], and smartphone use [24]. Numerous studies have shown associations between objective behavioral and physiological features collected via MS and depression [25]. However, few studies covered longer time spans that allow for the modelling of depressive illness processes within individuals over the life span. In a recent systematic review [26], we found only nine studies that had collected MS data from patients with depressive disorders for time-spans of 12 weeks or more. One study showed that sleep features (sleep architecture, sleep stability, sleep quality, insomnia, and hypersomnia) collected using a Fitbit device were associated with a worsening of the functional depressive status over the following two weeks [27]. Six out of nine studies included in our systematic review demonstrated predicting capabilities of data on activity (step count, heart rate), sleep (including circadian rhythm), communication (call logs, messaging), phone usage (screentime), and location (Global Positioning System, GPS) for depressive episodes and/or symptom severity [[28], [29], [30], [31], [32], [33]]. Based on MS data, a predictive accuracy for depression from 79 % to 91 % has been achieved [26]. One study in particular showed that in adolescents, personalized models to predict depression severity from MS data achieved better results than universal models [32]. To our knowledge, this result has not yet been replicated for adult patients with depressive disorders.

In summary, patients with depressive disorders need objective markers to monitor their illness severity and reliable, valid models to predict clinically meaningful changes in the severity of their condition. This is essential as symptom presentations can vary greatly within individuals over time [34], and those with depressive disorders experience fluctuations in both positive and negative affect [35]. Objective markers could support patients in the self-management of their illness and predictive models could inform health professionals concerning treatment decisions. As phenotypes of depression vary greatly, these markers and predictive models need to be made-to-measure for each patient. Using MS, patients can unobtrusively collect enough personal data to facilitate the creation of personalized models for data analysis. To our knowledge, however, no study has shown that personalized models based on MS data can serve as objective markers of individual illness severity or forecast depression severity for individual patients. Therefore, the current study aims to achieve a proof-of-concept showing that personal MS data can (I.) monitor and (II.) predict depression severity in individual patients. To this end, adult participants with depressive disorders will collect continuous, daily data on sleep/deep rest, physical activity (locomotion, heart rate), speech features, smartphone usage (including digital communication behaviour) as well as self-reported depressive symptom severity over the course of one year using AA methods. With this data, we aim to answer the following exploratory research questions (RQ):I.a) Are personal behaviour (sleep/deep rest, physical activity, smartphone usage) and physiology (heart rate, heart rate variability, speech) during daytime (6 a.m.–6 p.m.) associated with self-reported depressed mood and anhedonia in the evening within adult patients with depressive disorders?b) Are personal behaviour (sleep/deep rest, physical activity, smartphone usage) and physiology (heart rate, heart rate variability, speech) during daytime (6 a.m.–6 p.m.) of the last 7 days associated with the weekly self-reported depression severity within adult patients with depressive disorders?II.a) Can individualized statistical models based on longitudinal data on personal behaviour (sleep/deep rest, physical activity, smartphone usage) and physiology (heart rate, heart rate variability, speech) forecast the self-reported depressed mood and anhedonia in the evening within adult patients with depressive disorders?b) Can individualized statistical models based on longitudinal data on personal behaviour (sleep/deep rest, physical activity, smartphone usage) and physiology (heart rate, heart rate variability, speech) predict the weekly self-reported depression severity within adult patients with depressive disorders?

## Methods

1

### Design

1.1

This exploratory study uses an observational n-of-1 design [36], involving repeated measurements of self-reported, behavioural, and physiological outcomes over the time of one year (365 days) within individuals without manipulation of variables by the investigators. The work is carried out in accordance with the World Medical Association Declaration of Helsinki [37]. Ethical approval has been granted by the Ethics Committee of the Department of Medicine at Goethe University Frankfurt, Germany (date: 24/08/2023, reference number: 2023–1309). The study protocol has been registered in the German Clinical Trials Register (reference number: DRKS00032618).

### Study population

1.2

We aim to collect 10–12 complete case studies of adult patients with depressive disorders; allowing for some dropout, *N* = 15 participants will be included. Patients are recruited at the Department of Psychiatry, Psychosomatic Medicine and Psychotherapy, University Hospital of Goethe University Frankfurt, Germany. This study protocol is presented to treating physicians and psychologists at various occasions and a flyer with the inclusion and exclusion criteria (see Table 1) is provided. Physicians and psychologists invite patients who are receiving treatment for affective disorders to participate in the current study. Interested patients provide their contact details and written consent to be contacted by the study centre. If sufficient participants can't be reached, various communication channels of the German Foundation for Depression and Suicide Prevention (e.g., newsletter, website, online discussion forum) shall be used to draw the attention of interested participants to the study.

**Table 1 tbl1:** Inclusion and exclusion criteria for study participation.

Inclusion criteria	Exclusion criteria
- Minimum 18 years old	- Acute risk of self-hazard/suicidality (six months before inclusion)
- Diagnosis of a recurrent major depression (ICD-10 F33) with two or more depressive episodes during the last ten years	- Currently severe depressive episode with psychotic symptoms (F33.3)
- Currently residual symptoms of depression (BDI-2 sum score ≥14)	- Lifetime diagnosis of any psychotic disorder (any diagnosis according to ICD-10 F2)
- Being in concurrent treatment for the depressive illness	- Lifetime diagnosis of any bipolar disorder (ICD-10 F31)
- Being able to provide informed consent	- Lifetime diagnosis of any borderline personality disorder
- Usage of an own Android smartphone (or agreement to switch to an Android smartphone provided by the study centre)	- Severe somatic illnesses requiring intensive treatment
- In case of any lifetime substance abuse disorder: being in stable remission (min. 6 months)	

Note: ICD-10 = International Classification of Diseases, Tenth Revision, BDI-2 = Beck Depression Inventory-II.

### Procedures

1.3

Eligible participants are screened for inclusion and exclusion criteria and then start with study participation. The participation in the study encompasses three major appointments at the study centre: Baseline (V0), 6-month follow-up (V6), and 12-month follow-up (V12). In between, shorter monthly appointments (V1-V5, V7-V11) are planned to assist in case of any technical difficulties, to assess data completeness with the participants, and to manage suicidality if necessary. Fig. 1 provides details of the timeline and study procedures.

**Fig. 1 fig1:**
[figure not shown]
Timeline of study procedures. Caption: At baseline (V0, time requirement: 3.5–4 h), participants read the participant information sheet, clarify any questions about the study with the study team, and provide written, informed consent for study participation. A standardized clinical interview (SCID-5) is conducted and several self-report questionnaires are filled in (see Measures section). After the assessments are completed, the participants are assisted in installing the iTrackDepression-App (iTD-App) via the Google PlayStore on their smartphone. The iTD-App has been developed by the German Foundation for Depression and Suicide Prevention in collaboration with adesso SE (Dortmund, Germany) and the InfAI Institute for Applied Informatics (Leipzig, Germany). It has two major components for the collection of depression-related data: self-report assessments and sensor technology. Additionally, participants are asked to continuously wear a Samsung Galaxy 5® smartwatch that is provided by the study centre to record data on physiological and behavioural parameters such as heartbeat and physical activity (please refer to Measures for a detailed description). Any technological questions are clarified before the participants start continuous data collection in their daily lifes. V1-V5 and V7-V11 are used to provide technical support, check for data completeness, and manage suicidality if necessary. These appointments can be conducted via video call or telephone, depending on the preference of the participants. At V6 (6-month follow-up), the BDI-II will be completed at the study centre and any changes in the treatment plan during the last six months are assessed. The final appointment (V12) is conducted after 12 months of study participation. At V12, the SCID-5 is repeated to assess for any psychiatric diagnosis during the year of study participation and the BDI-II will be completed to check and record the participants' status at the end of the study. Changes in the treatment plan during the study participation are assessed and recorded. The Samsung Galaxy 5® smartwatch is returned to the study team and any final questions are answered. Note: MONDY is the name of the overarching project: “MONDY: Secure and open platform for AI-based healthcare apps”, see Funding information.

Data completeness is monitored continuously by the study centre, supported by a custom application that provides metadata on daily questionnaire completion and duration of smartwatch wearing. Participants are contacted by the study centre if they have made less than one entry in the iTD-App or have worn the smartwatch for less than 10 h per day for three consecutive days. If the issue can't be resolved via phone, e-mail, or videocall, participants are invited for an in-person meeting at the study centre to resolve any issues. Participants receive a compensation of 200 Euro for their participation in the study (€15 per completed month, plus an additional €20 upon completion of V12 and return of the smartwatch).

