#### Premature study termination (dropout)

1.3.2

Participation in the study is voluntary. Participants can decide to opt-out of the study at any time without providing any reasons. In case that the participation of a participant ends prematurely, all procedures of V12 are brought forward to a final assessment. If a participant is not able to complete V12, only a short meeting is scheduled to return the smartwatch and complete the BDI-II questionnaire.

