##### Daily self-report

1.4.2.1

In the morning and evening assessments, well-being (mood, tension, exhaustion, rumination) and sleep in the previous night are assessed. In the evenings, daily self-reported depressive symptom severity is assessed using the Patient Health Questionnaire-2 (PHQ-2 [43]), a very short measure assessing two core symptoms of depression (loss of interest/joylessness and feeling down/depressed/hopeless). Following previously established procedures [15,16], answers are given on a Visual Analogue Scale ranging from 0 to 10 with labelled endpoints (0 = never, 10 = all the time). Additionally, contextual information is queried to facilitate the interpretation of the data (substance use, medication, daytime activities).

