### Data analysis

1.6

The current study does not encompass confirmatory hypothesis testing and has explorative character, aiming to provide proof-of-concept for the value of personalized monitoring and forecasting of depression severity in individual patients. Missing data will be handled with model-specific imputation when needed.

To answer RQI, i.e. “Can personal MS data be an objective marker of the a) daily and b) weekly self-reported depressive symptom severity?“, we will conduct multilevel correlations between depressive symptom severity (PHQ-2, PHQ-9) and features derived from MS data through the application of data-driven methods. Multilevel approaches can be applied for statistical analyses of idiographic data [49,50]. Multilevel correlations will include participants as fixed effects and as random effect. All MS features will be included in the mixed model as fixed effects. However, in multilevel models, within-person variability is pooled across individuals, rather than person-specific [51]. Therefore, we will repeat analysis for each participant separately (truly idiographic *N* = 1 version of the analysis) to understand whether there are any differences in results if the data base is limited to MS features derived from personal data of the individual only. Apart from the correlations themselves, the effect sizes will be assessed to understand the clinical relevance of associations and a Random Forest classifier will be used to account for non-linear associations and to asses feature importance using Kernel SHAP analysis [52]. To validate our findings on an idiographic level, we will explore the use of unified structural equation modelling (USEM, [53,54]), including Group Iterative Multiple Model Estimation (GIMME; [55,56]) that can estimate both group-level relationships and individual-specific relationships.

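### All participants are under treatment, but no RQI or VAR analysis names a treatment term, so a treatment change that shifts both sensors and mood can appear as a within-person association with no day-to-day link

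*Protocol article*

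**What the plan says.** Table 1 (section 1.2) makes treatment an entry condition: "Being in concurrent treatment for the depressive illness". The Fig. 1 caption places the assessment of treatment changes at two visits. At V6, "any changes in the treatment plan during the last six months are assessed". At V12, "Changes in the treatment plan during the study participation are assessed and recorded". The ten contacts in between have other purposes: "V1-V5 and V7-V11 are used to provide technical support, check for data completeness, and manage suicidality if necessary".

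Two app items bear on the same question. In the evening self-report (section 1.4.2.1), "contextual information is queried to facilitate the interpretation of the data (substance use, medication, daytime activities"). Section 1.4.2.2 adds a weekly question on special events with optional free text.

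For participants who leave early, section 1.3.2 brings all V12 procedures forward. If V12 cannot be completed, "only a short meeting is scheduled to return the smartwatch and complete the BDI-II questionnaire".

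For RQI, section 1.6 names participants and sensor features as model terms: "All MS features will be included in the mixed model as fixed effects". The analysis is then repeated for each participant separately. For RQII it plans idiographic VAR models with impulse responses and variance decomposition, validated forward in time. For both questions a sensitivity analysis compares all ambulatory data with sensor data alone. Treatment is not mentioned in section 1.6. Section 1.3.3 gives 2 December 2024 as last patient out.

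**The concern.** Participants have residual symptoms, are recruited at a university psychiatry department and are followed for 365 days. A change of drug, psychotherapy or care setting during that year is foreseeable, and the protocol expects it enough to ask about it. In an N-of-1 series such a change may act as a level shift. It can move the PHQ score and, at the same time, heart rate, sleep, steps and phone use.

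RQI a) asks whether daytime behaviour and physiology go with depressed mood and anhedonia the same evening, within the person. One shared level shift can produce that correlation even if, within each treatment phase, today's sensor values say nothing about this evening's mood. A reader cannot tell the two situations apart from the unadjusted coefficient.

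For RQII, a VAR in its standard form assumes stable dynamics. Fitted across a change, its impulse responses average over two regimes. In forward-in-time validation, a model trained under one treatment and tested under another may forecast poorly for that reason alone, and the result could be taken as evidence that sensor data do not predict.

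**Working it through.** The article gives no power, alpha or effect size for this point, so there is no figure of its own to reproduce. The calculation below only illustrates size.

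**Inputs.** From the protocol: 365 daily values (section 1.1) and about 52 weekly values (365/7). Assumed: a shift of d within-phase SDs in both the feature and the PHQ score, lasting for a share p of the year; no association within phases; no autocorrelation.

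**Daily data.** A step of size d present for a share p adds p(1−p)d² to each variance and, in absolute value, to the covariance. Hence

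|r| = p(1−p)d² / [1 + p(1−p)d²].

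For p = 0.5 and d = 0.8: 0.25 × 0.64 = 0.16, and 0.16/1.16 = 0.14.

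| Share p | d = 0.5 | d = 0.8 | d = 1.0 |
|---|---|---|---|
| 0.5 (mid-year) | 0.06 | 0.14 | 0.20 |
| 0.25 | 0.04 | 0.11 | 0.16 |
| 0.1 (about five weeks) | 0.02 | 0.05 | 0.08 |

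For scale, a nominal 5% test on 365 points needs |r| of about 1.96/√362 = 0.10. By Fisher's z, a mid-year step gives a nominally positive result in about 20%, 75% and 97% of such participants for d = 0.5, 0.8 and 1.0. At d = 0.8, for example, atanh(0.138) × √362 = 2.64, and P(Z > 1.96 − 2.64) = 0.75. Simulation agrees.

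**Weekly data.** The 5% threshold on 52 points is about 1.96/√49 = 0.28. If the shift is d in the SD of the weekly series, the mid-year values above (at most 0.20) stay below it. RQI b) uses features from the last seven days. If these are averaged (an assumption), the feature noise variance falls to 1/7 and the step stays, so

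|r| = 0.25d² / √[(1 + 0.25d²)(1/7 + 0.25d²)],

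which is 0.27 for d = 0.8 and 0.36 for d = 1.0. The weekly result therefore depends on how the features are built.

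**What a phase term does.** In simulation with a mid-year step, regressing both series on a correctly dated step returns the positive rate to about 5%. With the date wrong by 30 or 60 days it is about 13% or 30% for d = 0.8, and about 23% or 55% for d = 1.0. The adjustment is thus only as good as the phase dates. These misdating errors are assumed and are not taken from the protocol.

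**The case against.** Several points on the other side stand.

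- A reader might infer that treatment changes are known only through six-month recall. The documents do not support this. The daily self-report queries medication, and the weekly life-event note could catch an admission. Fig. 1 does not say whether the visit assessment relies on memory or on records, nor that dates are left out. The exact wording of the daily items is in a supplement that is not shown. What remains is that the article describes no dedicated dated item for psychotherapy or care setting.
- A reader might infer that early leavers lose this information. By default they receive all V12 procedures; the short meeting is the fallback.
- A reader might infer that treatment data enter no model at all. The comparison of all ambulatory data with sensor data alone may bring self-report items in, although the article does not say that medication is among them. A full covariate list may also sit in an analysis plan.
- A reader might infer that a treatment effect will be mistaken for a behavioural marker. That is too certain. RQI asks about association, not causation. A sensor that follows mood when treatment works may be a valid monitoring marker, and adjusting for phase could remove real signal.
- The mid-year step maximises p(1−p), and the study does no confirmatory testing, so the positive rates describe bias and are not an error-rate claim.
- Section 2.1 concedes that context may be incompletely captured and that patterns may not generalise beyond the study year. It does not address a change of regime within that year.

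These points narrow the concern. They do not remove the need to separate a shared level shift from a day-to-day link.

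**Conclusion.** The point holds as a possibility that the analysis described cannot rule out. Treatment is universal in the sample, treatment-plan changes as such are assessed only at V6 and V12 with partial support from the app, and no treatment term is named for the RQI models or the VAR and impulse-response work. Under the assumptions above, a lasting mid-year shift of 0.5 to 1.0 SD in both series gives a daily correlation of about 0.06 to 0.20 with no day-to-day link. A five-week phase gives 0.02 to 0.08. How often such changes occurred, and how large they were, cannot be known from the article. For RQII the consequence is qualitative: regimes may be mixed in the VAR results, and training and test periods may fall under different treatments. A sensitivity analysis on data already collected is proportionate.

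**What to change.** Data collection has ended, so the change is to the analysis.

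1. Build dated treatment phases for each participant from the V6 and V12 records, the daily medication entries and the weekly life-event notes. Do this before looking at the associations.
2. In section 1.6, for RQI, add a sensitivity analysis that reports the N = 1 and multilevel associations with and without a step term at each dated treatment change. Keep the unadjusted result in the report.
3. In section 1.6, for RQII, enter phase as an exogenous term in the VAR models as a sensitivity analysis, and report forecast error separately for test periods before and after a change.

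The cost is assembling the phases from existing records and one indicator per change. Some precision is lost in participants with several changes, and phase dates for non-drug treatment may be imprecise, which leaves part of the shift unadjusted. An association carried only by a treatment change will shrink in the adjusted result; showing both results lets the reader judge it.

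For a successor study only: the protocol states that "shorter monthly appointments (V1-V5, V7-V11) are planned to assist in case of any technical difficulties", and a dated question on treatment changes could be added to such contacts. It can no longer help this cohort.
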